### Study visits and assessment

Study duration will be 50 weeks, comprised of a 2-week run-in period, 24 weeks of intervention, and 24 weeks of follow-up. After treatment commences, visits will occur every 4 weeks during the intervention period. During the follow-up period, participants will be asked to visit at 28, 36, and 48 weeks. An overview of specific measurements and time points of data collection can be found in Table 3.

**Table 3 Tab3:** Schedule of enrollment, allocation, visits, and assessments

	Study Period										
	Enrollment	Allocation	Intervention						Follow-up		
Time point (weeks)	−2	0	4	8	12	16	20	24	28	36	48
Eligibility screen	√										
Written informed consent	√										
Medical history	√										
Physical examination		√	√	√	√	√	√	√			
Routine blood and urine		√		√		√		√			
Electrocardiogram		√		√		√		√			
ALT, AST, ALP, GGT, TBIL		√		√		√		√			
24 h urinary protein		√	√	√		√		√	√	√	√
Serum Cr, eGFR		√	√	√		√		√	√	√	√
TC, TG, LDL-C, HDL-C		√	√	√		√		√			
A1C, CRP		√		√		√		√			
Evaluation of TCM syndrome		√	√	√	√	√	√	√	√	√	√
Drug distribution		√	√	√	√	√	√				
Retrieval of unused drugs			√	√	√	√	√	√			
Adverse events			√	√	√	√	√	√	√	√	√

*Abbreviations*: *A1C* hemoglobin A1C, *ALP* alkaline phosphatase, *ALT* alanine transaminase, *AST* aspartate aminotransferase, *eGFR* estimated glomerular filtration rate, *GGT* gamma-glutamyl transpeptidase, *LDL-C* low-density lipoprotein cholesterol, *serum Cr* serum creatinine, *TBIL* total bilirubin, *TC* total cholesterol, *TCM* traditional Chinese medicine, *TG* triglycerides, *HDL-C* high-density lipoprotein cholesterol

√ = Action items

### Outcome measurements

#### Primary endpoint

The primary endpoint is 24 h UP. The change in 24 h UP from baseline to 24 weeks will be the analysis metric for the difference between the two groups. At baseline and treatment endpoint (24 weeks), the average values of two different samples collected within 1 week will be used to minimize variation between the different urine samples.

#### Secondary endpoints

Secondary endpoints will be as follows:Change in serum creatinine (SCr) and eGFR (2009 CKD-EPI creatinine equation [25]) from baseline to 24 weeksChange in blood lipid profile of total cholesterol (TC), triglyceride (TG), high-density lipoprotein cholesterol (HDL-C), and low-density lipoprotein cholesterol (LDL-C) from baseline to 24 weeksImprovement in TCM symptoms (evaluation by TCM symptom score scale) from baseline to 24 weeksSafety assessment: Results of routine blood and urine tests, electrocardiogram (ECG), alanine aminotransferase (ALT), aspartate aminotransferase (AST), alkaline phosphatase (ALP), gamma-glutamyl transpeptidase (GGT), and serum total bilirubin (TBIL) tests will comprise the comprehensive safety assessment. The safety endpoints will include the incidence and severity of drug-induced liver injury (DILI) and bone marrow suppression (BMS), as well as the incidence of QTc prolongation, as measured by ECG. DILI is defined by criteria established by the International Serious Adverse Events Consortium [26]. The causality relationship between DILI and the intervention drug will be assessed with the Roussel Uclaf Causality Assessment Method (RUCAM) [27]. Severity is scored on a range from 1 (mild) to 5 (fatal) [28]. The diagnosis and severity of bone marrow suppression will be assessed by criteria established by the World Health Organization Collaborating Centre for International Drug Monitoring [29]: grade I: white blood cell (3.0–3.9) × 109/l, hemoglobin 95–100 g/l, platelet (75–99) × 109/l; grade II: white blood cell (2.0–2.9) × 109/l, hemoglobin 80–94 g/l, platelet (50–74) × 109/l; grade III: white blood cell (1.0–1.9) × 109/l, hemoglobin 65–79 g/l, platelet (25–49) × 109/l; grade IV: white blood cell (0–1.0) × 109/l, hemoglobin < 65 g/l, platelet < 25 × 109/l. QTc longer than 0.44 second is regarded as prolongation.

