Constipation	□ 0: None □ 1: Hard stools and straining □ 2: Hard stools with a 2 to 3 days between bowel movements □ 3: Hard stools with 3 or more days between bowel movements
Hematuria	□ 0: None □ 1: Yes

After being screened for inclusion and exclusion criteria (Table 2), eligible patients will be entered into the trial.

**Table 2 Tab2:** Eligibility criteria

Inclusion criteria	Exclusion criteria
• DKD diagnostic criteria: a) Type 2 diabetes b) Diabetic retinopathy c) 24-h urinary protein (24 h UP) 0.5–3.5 g • Serum creatinine <265 μmol/L (3 mg/dl) • Controlled hypertension (blood pressure ≤ 130/80 mmHg) • A1C ≤ 8.0 • Chinese syndrome differentiation of *qi* and *yin* deficiency with blood stasis • Taking irbesartan (300 mg daily) continuously in the past 2 weeks • Between 18 and 70 years of age • Sign informed consent	• Blood pressure < 90/60 mmHg • Serum potassium > 5.5 mmol/L or < 3.5 mmol/L • Doubling of serum creatinine in the past 6 months • Renal artery stenosis • Severe diabetes complications or serious macrovascular events within 6 months (e.g., cerebral hemorrhage, massive cerebral infarction, or acute myocardial infarction) • Recent infection in the past 4 weeks • Other primary or secondary renal diseases (e.g., IgA nephropathy, membranous nephropathy, or lupus nephritis) • Any malignancy • Severe mental disorder • Pregnant or lactating women or women with the intention of becoming pregnant or women who are not using appropriate contraceptive methods • Allergic to components of agents used in the study • Participation in other clinical trials

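### Bone marrow suppression and QTc prolongation are defined by absolute cut-offs that ignore the week-0 value, so unchanged pre-existing abnormality can be counted and can dilute a safety difference

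*Protocol article*

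**What the plan says.** All references are to the protocol article.

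- **Endpoints.** For liver injury and marrow suppression, the Secondary endpoints section states: "The safety endpoints will include the incidence and severity of drug-induced liver injury (DILI) and bone marrow suppression (BMS"). For QTc it names incidence only, read from the ECG.
- **QTc rule.** "QTc longer than 0.44 second is regarded as prolongation". There is no change-from-baseline term.
- **BMS rule.** Four grades set by absolute bands, the lowest being "grade I: white blood cell (3.0–3.9) × 109/l, hemoglobin 95–100 g/l, platelet (75–99) × 109/l". Grade III white cells run from 1.0 to 1.9 and grade IV from 0 to 1.0 (× 10⁹/l).
- **Contrast in the same section.** Creatinine, eGFR, lipids and TCM symptoms are each framed as change or improvement from baseline to 24 weeks.
- **Eligibility (Table 2).** "Serum creatinine <265 μmol/L (3 mg/dl") is admitted. No haemoglobin, blood-count or QTc limit is listed.
- **Schedule (Table 3).** The rows "Routine blood and urine" and "Electrocardiogram" are both ticked at weeks 0, 8, 16 and 24.
- **Statistical analysis.** BMS is tested by Kruskal-Wallis and QTc by chi-square, with no baseline term. The safety set is randomised participants with at least one visit.

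**The concern.** A participant with haemoglobin 98 g/l or QTc 0.45 s at week 0, and the same value at every later visit, meets the written definition of grade I BMS or of QTc prolongation. Nothing about that participant has changed on treatment. The entry criteria do not keep such people out, the safety set does not remove them, and the planned tests do not adjust for them. A formal causality method (RUCAM) is named for drug-induced liver injury but not for these two endpoints.

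Cases that precede the first dose carry no information about the drug. Counted in both arms, they shrink the risk difference and add noise. In an efficacy comparison that loss would be conservative. In a safety comparison it leans towards a reassuring null, and the Background says the trial is meant to establish whether TSF is safe as well as efficacious.

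**Working it through.** **No figure to reproduce.** The article gives no event rate, power or sample size for BMS or QTc. The trial is sized on 24 h urinary protein alone. What follows only illustrates scale.

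**Inputs from the article.** N = 144 at 1:1, so 72 per arm (Sample size estimation); significance at 0.05, taken as two-sided; chi-square for QTc (Statistical analysis).

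**Assumed inputs, not in the article.**
- b: share already beyond the cut-off at week 0, the same in both arms and persisting to later visits.
- q₁ and q₀: risk of new onset in the TSF and placebo arms among those normal at week 0.

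**Two ways of counting.**

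1. Any value beyond the cut-off: p = b + (1 − b)q, with 72 per arm. The risk difference is p₁ − p₀ = (1 − b)(q₁ − q₀), so it shrinks by the factor (1 − b).
2. New onset only, among those normal at week 0: risks q₁ and q₀, with m = 72(1 − b) per arm, rounded.

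**Example with b = 20 %, q₁ = 20 %, q₀ = 5 %.**
- Any value: p₁ = 0.20 + 0.80 × 0.20 = 0.36; p₀ = 0.20 + 0.80 × 0.05 = 0.24. The difference falls from 15 to 12 points.
- New onset: 20 % v 5 % with m = 72 × 0.80 = 57.6, rounded to 58 per arm.

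**Power**, from exact enumeration of the two binomials and an uncorrected two-sided chi-square test at 0.05:

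| New-onset risk | b | Any value | New onset only (m per arm) |
|---|---|---|---|
| 20 % v 5 % | 0 | 81 % | 81 % (72) |
| | 2 % | 74 % | 80 % (71) |
| | 10 % | 52 % | 77 % (65) |
| | 20 % | 35 % | 72 % (58) |
| | 40 % | 20 % | 61 % (43) |
| 10 % v 2 % | 0 | 55 % | 55 % (72) |
| | 10 % | 22 % | 50 % (65) |
| | 20 % | 15 % | 45 % (58) |
| | 40 % | 9 % | 37 % (43) |
| 5 % v 1 % | 0 | 26 % | 26 % (72) |
| | 10 % | 10 % | 23 % (65) |
| | 20 % | 8 % | 19 % (58) |

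The direction is the same throughout. The gap closes as b approaches zero. With a small true effect (5 % v 1 %), both rules would usually miss it.

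**Limits of the illustration.** It matches the planned QTc test. BMS is to be analysed by Kruskal-Wallis, so the same mechanism applies but these powers do not carry over exactly.

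**Band overlap.** A white-cell count of exactly 1.0 × 10⁹/l falls in both grade III and grade IV. This affects the severity grade at one value; it cannot change whether a participant is a case.

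**The case against.** The strongest reply is that the article never says week-0 abnormalities count. Incidence ordinarily can mean new cases, and suppression and prolongation read naturally as things that develop on treatment. A treatment-emergent rule is often left to the SAP or to the full protocol, neither of which is shown, and the week-0 counts and ECGs are just what such a rule would need. That stands in part: a reader might infer that the plan does count pre-existing cases, and the text does not establish it. What remains is that the article does not leave the case definition open. It fixes the grades, the cut-off and the tests, and as written they do not refer to week 0.

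A reader might also infer that the rule hides a real treatment signal or biases the comparison. The documents do not support that. Pre-existing cases are expected equally in both arms, so the consequence is dilution, and its size depends on a prevalence and on event risks that the article does not give. No power is claimed for these endpoints.

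There is other safety review as well. Each adverse event is assessed for its relation to the study drugs and reported with grade and time of occurrence, so a marrow or QTc effect would not have to surface through one incidence test alone. That is true, but it does not define these two endpoints.

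Finally, the overlap at 1.0 is trivial, and the bands are attributed to a cited source. Agreed; it is noted only for tidying.

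**Conclusion.** The point holds as one of definition. The BMS and QTc rules do not use the week-0 value although it is collected, and nothing in eligibility, the safety set or the planned tests compensates. Applied literally, they can count unchanged pre-existing abnormality and so dilute a true between-arm difference. They create no false difference.

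The size cannot be fixed from the article. The loss could be large, with roughly half the power gone in the 20 % prevalence example, or negligible if few participants start beyond the cut-offs. All of this assumes equal week-0 prevalence in the arms and persistence of the abnormality. The importance is low: these are secondary safety endpoints and one clarification settles the matter.

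**What to change.** Amend the analysis definitions and leave the cited thresholds as they are:

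- Count a BMS event only when the grade is worse than the same participant's grade at week 0.
- Count QTc prolongation only among participants whose QTc was at or below 0.44 s at week 0.
- Also report QTc change from week 0 by arm, so that participants already above the cut-off still contribute.
- Reconcile the grade III and grade IV white-cell bands at 1.0 with the cited source.

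If new onset was always intended, the first two items simply say so. The cost is about two sentences; the week-0 counts and ECGs are already scheduled. The downside is a slightly smaller denominator for QTc incidence (58 instead of 72 per arm in the 20 % example).

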#### Additional measurements

Tests for A1C and serum C-reactive protein (CRP) will be carried out at study visits 4, 8, 16, and 24 weeks.

#### Adverse events

Adverse events (AEs) such as signs and symptoms and other ailments will be documented at every study visit. Each AE will be classified as a mild, moderate, or severe AE, and its correlation with the intervention drugs will be assessed. Severe AEs will be reported to the principal investigator and the ethics committee within 24 h. All the adverse events will be recorded, monitored, and treated until properly resolved.

### Quality control of laboratory specimens

To eliminate potential discrepancies resulting from the handling of laboratory specimens by different labs, which may compromise data quality, samples collected at patient visits from all five participating medical centers will be cold-chain transported to a single laboratory (KingMed Diagnostics, Guangzhou) for processing. Data from KingMed will be quality controlled and securely transmitted in batches via e-mail back to participating sites and the principal investigators.

Blood and urine samples will be collected on site by a trained phlebotomist using standard techniques. The serum of each blood sample will be separated by centrifugation (3000 g, 15 minutes, 4 °C). Samples will be analyzed by an automated biochemistry analyzer (Roche Modular P800, Roche Diagnostics, Lewes, UK) using validated commercial kits. The 24 h UP and CRP will be assayed by immunoturbidimetry. Serum levels of sodium, potassium, and chlorine will be detected by ion-selective electrode methodology. Bilirubin will be determined by the diazo method. ALT, AST, ALP, and GGT will be measured by the velocity method. A direct method will be used for the quantitative determination of LDL-C and HDL-C. An enzymatic method will be used to assay SCr and TG. Cholesterol will be measured by the cholesterol oxidase method.

### Sample size estimation

The sample size was estimated based on results from our preliminary trial. These results found that after a 24-week treatment period, the mean reduction in 24 h UP in the placebo group was 0.40 ± 0.91 g; the mean reduction in 24 h UP in the TSF group was −0.31 ± 0.95 g. The least-squares mean of the difference value between the relative changes from baseline (TSF group-placebo group) was −0.54. The proportion of the cases between the TSF group and placebo group will be 1:1. With 80 % power to detect and a two-sided level of significance of 0.05, the sample size was estimated to be 54 in each group. In order to increase the accuracy of the data obtained, this number was increased to 60. Assuming a dropout rate of 20 %, the final sample size was estimated to be 144.

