**Methods/design:**

This trial is a five-center, randomized, double-blind, placebo-controlled study. DKD patients with a 24-h urinary protein (24 h UP) level between 0.5 and 3.5 g and serum creatinine < 265 μmol/L (3 mg/dl) will be included. A sample size of 144 participants will be randomly distributed into the treatment group (TSF plus irbesartan) and the control group (placebo plus irbesartan) at a ratio of 1:1. The study duration will be 50 weeks, comprising a 2-week run-in period, 24 weeks of intervention, and 24 weeks of follow-up. The primary endpoint will be the 24 h UP. Secondary endpoints will be an evaluation of renal function, management of blood lipids, improvement in traditional Chinese medicine symptoms, and safety assessments. Adverse events will also be evaluated.

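### The 20 % dropout allowance is multiplied on instead of divided out, so 144 randomized leaves about 57.6 per group, not the 60 it was built from

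*Protocol article*

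**What the plan says.** The Sample size estimation section takes three steps.

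1. A power calculation ("With 80 % power to detect", "a two-sided level of significance of 0.05", 1:1 allocation) gives 54 per group.
2. A voluntary increase follows: "In order to increase the accuracy of the data obtained, this number was increased to 60".
3. A dropout allowance closes the paragraph: "Assuming a dropout rate of 20 %, the final sample size was estimated to be 144".

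The Methods/design part of the Abstract shows that 144 counts participants at randomization: "A sample size of 144 participants will be randomly distributed into the treatment group" and the control group, 1:1, so 72 per group. No other section gives a different dropout adjustment.

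**The concern.** An allowance for dropout exists to preserve the number that stands before it. Here that number is 60 per group, and the stated rate is 20 %. A dropout rate is a fraction of those who enter, so the target has to be divided by the fraction retained (0.80). Adding 20 % of the target to itself gives too few. If that was done, 60 per group and 20 % dropout do not fit together at 144 randomized.

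The consequence is one of planning. Anyone judging retention during the trial would think that 20 % loss still leaves 60 per group, when it leaves fewer. Part of the margin added for accuracy would be gone at the very dropout rate that the plan assumes.

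**Working it through.** **Inputs**, all from Sample size estimation unless noted: 54 per group from the power calculation; 60 per group after the increase; dropout d = 0.20; final total 144; 144 is the number randomized (Abstract).

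**Reproducing 144**

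| Start per group | n × (1 + d) | n / (1 − d) |
|---|---|---|
| 60 | 60 × 1.2 = 72, total **144** | 60 / 0.8 = 75, total 150 |
| 54 | 54 × 1.2 = 64.8, rounded up to 65, total 130 | 54 / 0.8 = 67.5, rounded up to 68, total 136 |

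Of these four routes, only multiplying 60 by 1.2 gives 144.

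**Forward check**

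- Expected remaining at 20 % dropout: 144 × 0.8 = 115.2, or 72 × 0.8 = 57.6 per group.
- Shortfall against 120: 120 − 115.2 = 4.8, about 5 participants (2.4 per group).
- Largest dropout that keeps 60 per group: 1 − 60/72 = 16.7 %.
- Largest dropout that keeps 54 per group: 1 − 54/72 = 25 %.
- Margin over 54: planned 60 − 54 = 6 per group; expected 57.6 − 54 = 3.6 per group.

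**Effect on power, anchored on the protocol's own statement**

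Take 80 % power at 54 per group, two-sided 0.05, as given. Under the normal approximation the standardized effect at 54 is 1.960 + 0.842 = 2.802, and it grows with the square root of n. Power is Φ(2.802 × √(n/54) − 1.960).

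- n = 57.6: 2.802 × 1.0328 = 2.894; Φ(0.934) ≈ 82.5 %.
- n = 60: 2.802 × 1.0541 = 2.953; Φ(0.993) ≈ 84.0 %.

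The difference is about 1.5 percentage points, and both values are above 80 %.

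**The case against.** **60 is not stated as a post-dropout number.** This is correct. The paragraph never says that 60 per group will remain or be evaluable, and it sets no precision target. A reader might infer that the protocol promises 60 evaluable per group; the text does not go that far. What stands is the natural reading of the sequence: 60 is fixed first and dropout is allowed for afterwards. Reading the 20 % as a share of the 60 (12 extra on 60) would make the loss 12/72 = 16.7 % of those randomized, which is not the usual meaning of a 20 % dropout rate.

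**The only number tied to power is 54.** Also correct, and it limits the point. Inflating 54 properly needs 136 in total, and 144 exceeds that. A reader might infer that the trial is underpowered or must enrol 150. The protocol's figures do not support this, since the 80 % target holds on average up to 25 % dropout.

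**Intention-to-treat with imputation.** The Statistical analysis section defines a set of all randomized participants and plans multiple imputation, so the number analysed need not fall to 57-58 per group. The article does not say which set is primary. Imputation does not restore all the information lost, and the plan chose to inflate for dropout, so the inflation should match its stated rate.

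**Power from the pilot figures.** A reader might combine the −0.54 with the pilot SDs of 0.91 g and 0.95 g (pooled √((0.91² + 0.95²)/2) = 0.930) and quote t-test power of about 87 % at 57-58 per group against 88 % at 60. The article does not support those levels. It gives −0.54 without a unit and describes it thus: "The least-squares mean of the difference value between the relative changes from baseline (TSF group-placebo group) was −0.54". Treating it as grams with SD 0.93 is an assumption, and those inputs give 47-48 per group for 80 % power, not the stated 54. The levels in the working are therefore anchored on the 80 % at 54.

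**Conclusion.** The dropout step is wrong as written. The stated total follows from 60 × 1.2 × 2, whereas preserving 60 per group at 20 % dropout takes 150. As planned, 144 leaves about 115 (57-58 per group).

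The size is small. The slip takes 2.4 of the 6 per group added voluntarily and lowers power by about 1.5 points, with the 80 % target intact. It does not call for more enrolment and does not touch the endpoint or the analysis.

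The conclusion rests on two things: that 60 is the number the allowance is meant to preserve, inferred from the order of the steps, and that 20 % refers to those randomized. The power figures also assume that 80 % holds exactly at 54 per group and use a normal approximation.

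**What to change.** Keep 144 and add no enrolment. Replace the closing sentence of Sample size estimation with, for example:

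> 144 randomized gives about 115 participants (57-58 per group) at 20 % dropout, which exceeds the required 54 per group; 60 per group is retained only if dropout is at most 16.7 %.

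The 144 in the Abstract stays as it is. If a power figure is added, base it on the 80 % at 54 per group, or label it as assuming that −0.54 is in grams with SD 0.93.

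The cost is one sentence in the protocol or analysis plan. The Trial status section reports 123 recruited with the trial ongoing, and the change does not alter recruitment. The stated retention becomes slightly less favourable.

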### Randomization and concealment

Randomization will be carried out by an independent clinical research organization (CRO) from the Beijing Qihuang Drug Clinical Research Center. The CRO will use a computerized random number generator to produce the randomization schedule employing permuted blocks of random sizes. Participants will be randomly assigned to either the control or the TSF group at a 1:1 allocation. The drug administrator at each participating medical center will enroll patients sequentially based on consultation order. The blocks should provide comparable numbers of participants in both groups at any time in the course of the trial. To ensure concealment, the block sizes will not be disclosed. The randomization list will be retained by the Beijing Qihuang Drug Clinical Research Center for the duration of the study.

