#### TCM syndrome pattern differentiation

The Chinese syndrome pattern differentiation type of deficiency of both *qi* and *yin* with blood stasis will be based on guidelines delineated in *Clinical Research of New Investigational Drugs in Traditional Chinese Medicine* [24]. The diagnostic standards are as follows:Primary signs and symptoms include fatigue, listlessness, weakness, and soreness of the low back and knees; heat sensation in the palms and soles; and dry mouth and throat.Secondary signs and symptoms include catching cold easily, pale complexion, irritability, numbness, edema, frequent urination at night, constipation, and hematuria.

Participants will be diagnosed with deficiency of both *qi* and *yin* with blood stasis syndrome if they have two or more of the primary signs/symptoms and at least two of the secondary signs/symptoms. Investigators at each center will administer a symptom assessment survey to every participant (Table 1). This will ensure standardized scoring across centers.

**Table 1 Tab1:** Traditional Chinese medicine (TCM) symptom assessment survey

Fatigue	□ 0: None □ 2: Cannot sustain heavy work □ 4: Can manage mild intensity work □ 6: Can only do daily activities
Weakness and soreness of the low back and knees	□ 0: None □ 2: Occasional □ 4: Need to alter body position for relief □ 6: Persistent pain, need to take pain medication
Heat sensation in the palms and soles	□ 0: None □ 2: Occasional □ 4: Desire to expose extremities □ 6: Desire to hold something cold
Dry mouth and throat	□ 0: None □ 2: Mild □ 4: Decreased saliva production □ 6: Severe thirst with constant need to drink fluids
Qi deficiency and listlessness	□ 0: None □ 2: Shortness of breath after mild activity □ 4: Shortness of breath after moderate activity □ 6: Unable to talk or catch breath even without activity
Catch cold easily	□ 0: No colds □ 1: At least 6 times per year □ 2: At least 10 times per year □ 3: 12 or more times per year
Pale complexion	□ 0: None □ 1: Mild □ 2: Moderate □ 3: Pale or dark yellow complexion
Irritability	□ 0: None □ 1: Occasional □ 2: Easily irritated, but able to gain self-control □ 3: Severe agitation, unable to gain self-control
Numbness	□ 0: None □ 1: Hands and feet □ 2: Limbs □ 3: Entire body
Edema	□ 0: None □ 1: Palpebral edema in the morning □ 2: Palpebral and lower limb edema □ 3: Extreme generalized edema (hyposarca)
Frequency of urination at night	□ 0: None □ 1: 2 times □ 2: 3 to 4 times □ 3: 5 times or more

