#### Concomitant treatments

Based on the 2013 American Diabetes Association (ADA) practice guidelines, all participants will receive standard treatments as follows:Irbesartan: Irbesartan will be selected as the basic treatment to lower proteinuria and protect renal function. All participants will take irbesartan orally at a dosage of 300 mg daily.Antihypertensive drugs: Participants with hypertension will receive antihypertensive drugs to maintain a blood pressure of ≤ 130/80 mmHg. Non-dihydropyridine calcium channel blockers or alternatively, beta blockers, will be the recommended drugs. If the blood pressure cannot be maintained at 130/80 mmHg by the combination of these two drugs, diuretics will be added.Blood glucose control therapy: The A1C of all participants will be controlled to ≤ 8.0 % throughout the trial. Metformin will be used for participants with eGFR above 60 ml/min. For participants with eGFR below 60 ml/min, oral repaglinide will be the alternative. For participants whose A1C cannot be controlled with oral agents, insulin will be used.Antilipemic agents: Participants with hyperlipidemia will receive atorvastatin.

Participants will also be instructed to follow a low-sodium diabetes diet, including a reasonable intake of calories, protein, carbohydrates, and fat. They will also be asked to exercise regularly. Administration of other medications will be at the discretion of the attending physician investigator and would not interfere with outcome assessments. Investigators will be instructed to record in the CRF the details of any additional/transformational drug or therapy, such as the name, dosage, and duration of administration.

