### Statistical analysis

This trial will use three analysis sets: the intention-to-treat set, which will regard all participants as randomized regardless of whether or not they received the randomized treatment; the per protocol analysis set, which will be restricted to participants who complete the 24-week treatment and/or have the primary endpoint measurement records of at least three time points during the study; and the safety analysis set, which will include randomized participants who have made at least one visit. Multiple imputation analysis will be performed to account for the effect of missing data. Partially missing data will be carried forward with the principle of the last observation carried forward (LOCF). A *P* value less than 0.05 will be considered significant. SAS 9.2 software (SAS Institute, Cary, NC, USA) will be used for analysis.

Continuous variables will be expressed as the mean (SD), and categorical variables, as numbers and percentages. To compare baseline data between the two groups, independent *t* tests (or the Mann–Whitney U test) will be used to analyze continuous data, and chi-square or Fisher exact test will be used for categorical data. Outcome analysis will be performed using *t* test for normally distributed data and rank sum test for non-normal distribution data. Considering that the baseline 24 h UP and/or A1C are essential for the progression of urinary protein, analysis of covariance (ANCOVA) using 24 h UP and/or A1C as covariates will be performed to analyze the 24 h UP reduction at 24 weeks. To investigate the effects of treatment and time course, repeated measures analysis of variance (ANOVA) will be applied to determine changes in the 24 h UP and eGFR at each visit. For safety endpoints, incidences of DILI and BMS will be analyzed by Kruskal-Wallis test, and the incidence of QTc will be evaluated by a chi-square test. For AE evaluation, all AEs will be reported including its grade, time of occurrence, duration, treatment, prognosis, and correlation with the intervention drugs. The chi-square test or Fisher exact test will be used to compare the incidence of AEs between the two groups.

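### Five centers enroll, rate symptoms and manage part of co-treatment, yet no named analysis includes center; adding it is a cheap improvement, and leaving it out does not inflate false positives

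*Protocol article*

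**What the plan says.** **Centers and allocation.** Study design and setting names five hospitals. Under Randomization and concealment, an independent research organization generates the schedule with permuted blocks of random sizes and keeps the list. For the centers, the section says: "The drug administrator at each participating medical center will enroll patients sequentially based on consultation order". It names no stratification factor. The only purpose it gives for the blocks is similar arm sizes as the trial proceeds; balance within a center is not mentioned.

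**What center teams do.** TCM syndrome pattern differentiation says: "Investigators at each center will administer a symptom assessment survey to every participant (Table 1"). Concomitant treatments sets common rules for irbesartan, blood pressure, glucose and lipids, and then adds: "Administration of other medications will be at the discretion of the attending physician investigator".

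**Analyses.** Statistical analysis gives a t test or rank sum test for outcomes. For 24 h UP, "analysis of covariance (ANCOVA) using 24 h UP and/or A1C as covariates will be performed". Repeated measures ANOVA covers 24 h UP and eGFR over the visits. Center appears in none of these.

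**The concern.** A multicenter outcome usually carries some between-center variation. Here it could come from patient mix, on-site urine collection, discretionary medication and, for the TCM score, different raters working on subjective items. A model without center leaves that variation in the error term.

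The consequence depends on a fact the article does not give:

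- **Blocks within center.** The design balances the arms inside each center, so center differences cancel from the treatment contrast. A test without center still counts them as noise. Its standard error is then too large and the test is conservative.
- **One trial-wide list.** Arm counts inside a center vary by chance. The test without center allows for this and stays valid, but it is less efficient than one with a center term.

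At stake is a modest amount of calibration and power, not the direction or credibility of a positive result.

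**Working it through.** **The plan's own figures.** The article gives no center-related figure. Its sample size section supplies the scale: "a two-sided level of significance of 0.05", "With 80 % power to detect", and 60 per group after rounding up, so 120 evaluable. It also states: "The least-squares mean of the difference value between the relative changes from baseline (TSF group-placebo group) was −0.54"; and "the mean reduction in 24 h UP in the placebo group was 0.40 ± 0.91 g", with SD 0.95 g in the TSF group. The pooled SD is √((0.91² + 0.95²)/2) = 0.930. If 0.54 is read as grams (no unit is given), then n = 2 × (1.960 + 0.842)² × (0.930/0.54)² ≈ 47 per group, not the stated 54. That mismatch is a separate matter and does not bear on this point.

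**Assumptions for the check.** Five equal centers of 24, and an effect of 0.515 SD, which gives about 80 % power at 60 per group. The share ρ of outcome variance lying between centers is not in the article, so I use 5, 10 and 20 %. For an ANCOVA, ρ is the share of the variance left after the covariates.

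**Case 1: blocks within center.** The true standard error is √(1 − ρ) times the one the unadjusted test uses.

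- Type I error without center = 2 × (1 − Φ(1.96/√(1 − ρ)))
- Standard error too large by the factor 1/√(1 − ρ)
- Noncentrality at ρ = 0: 0.515/√(2/60) = 2.821
- Power without center = Φ((2.821 − 1.96)/√(1 − ρ))
- Power with center = Φ(2.821/√(1 − ρ) − 1.96)

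| ρ | Type I error, no center | Standard error too large by | Power, no center | Power, with center |
|---|---|---|---|---|
| 5 % | 4.4 % | 2.6 % | 81.1 % | 82.5 % |
| 10 % | 3.9 % | 5.4 % | 81.8 % | 84.5 % |
| 20 % | 2.8 % | 11.8 % | 83.2 % | 88.4 % |

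Simulating this setting gives type I error of about 4.7 / 3.8 / 3.1 %. Across runs the values lie at 4.4–4.8, 3.7–4.3 and 2.8–3.5 %, depending mainly on whether center differences are held at exactly ρ or drawn afresh in each trial. With center in the model, simulated type I error stays near 5 %.

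**Case 2: one trial-wide list.** Without center, simulated type I error was 4.8 to 5.2 % for ρ from 0 to 20 %. Power stays at Φ(2.821 − 1.96) = 80.5 %. Adding center uses up on average 4/119 = 3.4 % of the information on treatment, through chance imbalance within centers, and removes the share ρ from the noise:

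- Power with center = Φ(2.821 × √((1 − 0.034)/(1 − ρ)) − 1.96)
- ρ = 0: 79.2 %, a loss of about 1 point
- ρ = 5 %: 81.2 %
- ρ = 10 %: 83.2 %
- ρ = 20 %: 87.3 %

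Simulated gains are about 0 to 0.5, 2 to 2.5 and 5 to 7 points at 5, 10 and 20 %. The break-even center share is about 3.4 %.

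**Sensitivity to the effect size.** With 0.54 and SD 0.930, power without center under a trial-wide list is 88.9 %. With center and blocks within center it is 90.4 / 91.8 / 94.5 % at the three shares, so the gains are of the same order.

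**The case against.** **This may be left to other documents.** A journal article often leaves stratification and model detail to the full protocol or the SAP, and neither is shown. This has weight: an unseen SAP may already include center, and silence on blocking is not in itself an error. But the article does not leave the model open. It lists the ANCOVA covariates, and center is not among them, so the point is a change to a stated model.

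**Center differences may be small.** All samples go to one laboratory, expressly to remove between-laboratory discrepancies. Irbesartan, the blood pressure and A1C limits and the main drug choices are common to all centers. Other drugs that could affect urinary protein or renal function are prohibited. The sentence on discretionary medication goes on to say that such drugs would not interfere with outcome assessments. One survey and uniform training cover symptom scoring. This stands and makes a low share plausible for 24 h UP. It is weaker for the TCM score, which each center's own investigators rate. The article has no data on either share.

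**Stronger readings that a reader might infer.**

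- *Allocation is run by the centers.* Not supported: the schedule is made and held centrally, and the quoted sentence is about enrollment.
- *The trial's P values and intervals will be wrong.* Not supported without condition. The article states no intervals, miscalibration arises only with blocks within center, and then it is conservative.
- *Center is confounded with treatment under a trial-wide list.* This is chance imbalance, and the nominal 5 % level already covers it.

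**Conclusion.** The point holds as a cheap improvement. The named analyses omit center in a five-center trial, and the article does not say how the blocks relate to centers. With blocks within center the cost is a conservative test and about 1, 2 to 3 and 5 points of power at center shares of 5, 10 and 20 %. With a trial-wide list the test is valid, and the power forgone is about 0, 2 and 5 points or somewhat more. Neither case shows false-positive inflation, and power without center stays at about the planned 80 % or above.

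These sizes rest on the assumed shares, equal centers and 120 evaluable participants. At a share of 5 % or less the gain is slight. The TCM score has most to gain, but its size cannot be worked out from the article.

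**What to change.** - Before unblinding, add center (five levels) as a fixed factor beside baseline 24 h UP in the primary ANCOVA. Do the same in the models for eGFR and the TCM symptom score. If an SAP already does this, it is enough to say so.
- State in Randomization and concealment whether blocks were formed within each center or along one trial-wide list. The recommended model is the same either way, so no change to the allocation procedure is needed with 123 of the planned 144 already recruited.

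**Cost.** Four degrees of freedom (118 residual without center, 114 with it, before other covariates) and no new data, since center is known for every participant. The downside is about 1 point of power if centers do not differ and the list is trial-wide. With blocks within center and no center differences, the loss is negligible.
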